## **Background**

Diverticulosis is an increasingly common ailment in the aging population. An estimated 25% develop acute diverticulitis (Biondo et al., 2012). The prognosis of acute diverticulitis is related to its severity measured according to the Hinchey classification. The mildest diverticulitis heals on its own, while mortality from diverticulitis that causes fecal peritonitis is high (Wasvary et al., 1999). Peritoneal inflammation caused diverticulitis usually leads to an emergency sigmoid resection and possible intestinal contents diversion

through the stoma. In contrast, milder forms of acute diverticulitis are usually treated conservatively with an intravenous antibiotic and abscesses are drained.

It has previously been recommended that patients with recurrent diverticulitis undergo elective sigmoid resection to avoid further problems with complicated diverticulitis (Rafferty et al., 2006). However, retrospective work has found that the most difficult diverticulitis episode is usually the very first one, and the occurrence of complicated diverticulitis decreases with the recurrence of diverticulitis (Chapman et al., 2006; Ritz et al., 2011). Second, elective surgery for complicated diverticulitis (e.g., abscess) has been recommended (Rafferty et al., 2006). However, this recommendation has also recently been questioned (Gaertner et al., 2013). On the other hand, elective sigmoid resection has been shown to improve quality of life in selected patients with either recurrent diverticulitis or complicated diverticulitis (Forgione et al., 2009; Pasternak et al., 2011).

Current knowledge of who should have elective sigmoid resection is very limited, is based on retrospective comparative series or prospective studies that lack a control group. To date, no randomized, prospective study comparing surgical treatment to conservative treatment in patients with a relative indication (recurrent diverticulitis, complicated diverticulitis, pain after acute diverticulitis) to elective sigmoid resection has been published. An extensive recent treatment recommendation for diverticulitis cannot provide definitive recommendations for the selection of patients for elective sigmoid resection due to the lack of randomized work (Andersen et al., 2012).

The main objective of the study is to investigate the effect of elective sigmoid resection on gastrointestinal quality of life by comparing surgical treatment to conservative treatment in a randomized prospective multicenter study. The secondary objective is to investigate recurrence, mortality, and surgical complications of diverticulitis.

## **Hypothesis**

Elective sigmoid resection improves quality of life and reduces recurrence of diverticulitis in follow-up.

## Intervention Groups

1. Selective sigmoid resection
2. Conservative treatment (lifestyle guidelines, fiber supplement)

## Study Patients

### Inclusion criteria

1. Repeat left-side colon diverticulitis (at least 3, within a 2 years period, at least one CT confirmed)
2. Previously complicated diverticulitis \* (excluding diverticulitis with only pericolic air)
3. Pain or persistent change in bowel movements after CT-confirmed left side diverticulitis of colon, which lasted for more than 3 months after acute treatment

\* Complicated diverticulitis refers to acute left side diverticulitis verified by computed tomography that is associated with fistula, stricture, intestinal abscess or free air outside the intestinal lumen.

### Exclusion criteria

1. Multimorbidity that prevents consideration for elective surgery
2. Contraindication to laparoscopy (e.g. anesthetic reason)
3. Colon stricture
4. Fistula (colocutan, colovesical, colovaginal, etc.)

5. Active cancer
6. Previous resection of the left colon or rectum
7. Acute diverticulitis that has not resolved (inflammatory values need to have returned to normal and fever has stopped)
8. Colonoscopy / sigmoidoscopy or colon computed tomography (virtual colonoscopy) has not been performed within 2 years of randomisation
9. Age <18 or > 75 years
10. Pregnancy
11. Inability to answer quality of life surveys (eg dementia, psychiatric illness, etc.)

## Randomization

The patient is randomized 1: 1 for either elective sigmoid resection or conservative treatment. Patients are stratified based on inclusion criteria so that there are equal numbers of patients from each inclusion group in both randomization groups. Randomization is done using a computer centrally from the Helsinki University Central Hospital (HUCH). In practice, the person performing the randomisation connects to the HUCH server via the Internet, which provides the researcher with information about the patient's randomisation group. Randomization is performed at an outpatient visit, after the patient has first given written consent to participate in the study. Based on the group, treatment is selected, i.e. the patient is either placed in a surgical queue for elective sigmoid resection or given lifestyle instructions as well as instructions on how to use fiber supplementation. Upon randomization, the patient completes SF-36 and GIQLI quality of life questionnaires. Patients are analyzed according to the intention-to-treat principle according to the original randomization group.

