## Outcomes

### Primary outcome

Gastrointestinal Quality of Life Index (GIQLI) - difference between 0 months and 6 months from randomisation.

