## The sample size

In previous publications, preoperative GIQLI has been 95-100 (SD 22) and postoperative GIQLI 112-114 (SD 19-22) (Forgione et al., 2009; Pasternak et al., 2011). The sample size calculation was made using these values, and the study aims to show a difference of 12 GIQLI points, the standard deviation being assumed to be 22 points in both groups. Using 0.05 alpha, 0.9 power, and 1: 1 allocation, a sample size per group of 60 patients is obtained. The sample size calculation was performed using G \* Power 3.1.5.1 (comparison of means, two-tailed, A priori). Approximately 10% of patients are estimated to disappear at follow-up, bringing the final sample size to a total of 133 patients.

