## Statistical analysis plan (amendment 5th Aug 2020)

Primary outcome and continuous secondary outcomes that are normally distributed will be compared using t-test and effect size will be reported as mean difference with 95% confidence interval (95%CI). Continuous secondary outcomes that were not normally distributed will be compared using Mann-Whitney U test and effect size will be reported as  $r (=Z/\sqrt{N})$  without 95%CI. Categorical secondary outcomes will be compared

using Fischer's exact test (if expected cases in one cell <5) or  $\chi^2$  test and effect size will be reported as odds ratios (OR) with 95% CIs. All outcomes will be analyzed using intention-to-treat principle where patients are analyzed in the group where they were randomized to.

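### Randomisation is stratified by inclusion group but the planned tests ignore the strata; adding the stratum to the continuous-outcome models is a free, modest gain in precision

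*Supplement*

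**What the plan says.** The Randomization section of the protocol sets 1:1 allocation, run centrally by computer, and states: "Patients are stratified based on inclusion criteria so that there are equal numbers of patients from each inclusion group in both randomization groups". The Study Patients section lists three inclusion criteria: repeated left-sided episodes, earlier complicated disease, and symptoms lasting beyond three months after an acute episode. There are therefore three strata.

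The only analysis plan is the section Statistical analysis plan (amendment 5 Aug 2020). It says:
- "Primary outcome and continuous secondary outcomes that are normally distributed will be compared using t-test";
- "Continuous secondary outcomes that were not normally distributed will be compared using Mann-Whitney U test";
- categorical outcomes are compared "using Fischer's exact test (if expected cases in one cell <5") or otherwise by a chi-square test, and "effect size will be reported as odds ratios (OR) with 95% CIs".

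None of these is given a stratum term or a stratified form, and no adjusted or sensitivity analysis is described. Intention-to-treat is the only design feature carried into the analysis.

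The primary outcome is "Gastrointestinal Quality of Life Index (GIQLI) - difference between 0 months and 6 months from randomisation". The sample size section adds that "the study aims to show a difference of 12 GIQLI points", with "the standard deviation being assumed to be 22 points in both groups".

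**The concern.** When arms are balanced within strata, differences between strata cancel out of the treatment contrast. A two-sample t-test does not know this and leaves those differences in its error variance. If the strata predict the outcome, the reported standard error exceeds the true one. The p-values are then too large, the intervals over-cover, and the precision that stratifying was meant to buy goes unused.

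It is reasonable to think that the strata carry some information here. Only the third inclusion criterion requires current symptoms, so starting GIQLI and room to improve may differ between groups. A stratification factor left out of the plan also leaves open a later choice between crude and adjusted results.

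**Working it through.** **Inputs.** From the sample size section: difference 12 points, SD 22 per arm, two-sided alpha 0.05, power 0.90, 60 per group. From Randomization and Study Patients: three strata, balanced between arms. Assumed, because the documents give no figure: R², the share of within-arm variance in GIQLI change that lies between strata.

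**The plan's own figure.** n = 2 × (1.960 + 1.282)² × 22² / 12² = 70.6, so 71 per group (72 with the t distribution). The stated 60 does not follow from the stated inputs; 60 per group gives about 84% power by the t calculation. That is a separate sample-size point. It is used here only as the baseline for power.

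**Formulas**, with balance within strata and a normal approximation:
- Unadjusted SE at 60 per group: 22 × √(2/60) = 4.017, and 12/4.017 = 2.988.
- Ratio of unadjusted to true SE: 1/√(1 − R²).
- Type I error of the t-test: 2 × [1 − Φ(1.96/√(1 − R²))].
- Power of the t-test: Φ((2.988 − 1.96)/√(1 − R²)).
- Power with the stratum in the model: Φ(2.988/√(1 − R²) − 1.96).

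| Assumed R² | CI too wide by | Type I error, t-test | Power, t-test | Power, with stratum |
|---|---|---|---|---|
| 0 | 0% | 5.0% | 84.8% | 84.8% |
| 0.02 | 1.0% | 4.8% | 85.0% | 85.5% |
| 0.05 | 2.6% | 4.4% | 85.4% | 86.5% |
| 0.10 | 5.4% | 3.9% | 86.1% | 88.3% |

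**Check by simulation.** 40,000 runs at 60 per arm, three equal strata, exact balance within strata. At R² 0.10 the t-test rejected a true null in 3.7% of runs, and power was 85.5% for the t-test against 87.8% for the model with the stratum. With strata of 50%, 20% and 30% the figures were 4.0%, 85.3% and 87.6%. The type I error of the adjusted model stayed at about 5%.

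**What each R² means in GIQLI points.** Take total SD 22 (variance 484) and three equal strata. If the stratum means of GIQLI change are evenly spaced by d, the between-stratum variance is 2d²/3 and the extremes differ by 2d. If one stratum differs from the other two by m, the between-stratum variance is 2m²/9. Setting each equal to R² × 484 gives:

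| R² | Extremes differ by (evenly spaced) | One stratum differs by |
|---|---|---|
| 0.02 | 7.6 | 6.6 |
| 0.05 | 12.0 | 10.4 |
| 0.10 | 17.0 | 14.8 |
| 0.20 | 24.1 | 20.9 |

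The target treatment effect is 12 points. The pre- to postoperative gain that the sample size section takes from earlier series is 12 to 19 points (100 to 112, up to 95 to 114). An R² of 0.10 thus already needs strata to differ in mean change by more than the target effect, and 0.20 needs about twice that effect. This is why the range is stopped at 0.10.

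**The case against.** The strongest reply is that little is at stake. The primary outcome is a change score, so stable differences in level between the inclusion groups cancel; only differences in how much the groups change can matter. This stands, and it caps the plausible size. A reader might infer that the strata must be strongly prognostic because they are defined by clinical course. The documents support only that they may differ. At R² 0.20 type I error would be 2.8% and intervals 12% too wide, but that requires the 21 to 24 point differences shown above.

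A second reply is that no planned power is lost: the trial was sized for an unstratified comparison of means, and the t-test's power rises slightly as the strata become more prognostic. This also stands. What is given up is extra efficiency. The shortfall of 60 against 71 or 72 per group should not be charged to this point.

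A third is that every figure concerns the t-test. Nothing was calculated for the Mann-Whitney, chi-square or Fisher comparisons, and a stratified odds ratio estimates a different quantity from the crude one, so it is not the same interval made narrower. This stands too, and it limits the claim on size to continuous outcomes compared by t-test.

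None of this answers the omission itself. The strata were built into the design, the plan does not use them, and using them costs almost nothing.

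**Conclusion.** The plan does not analyse the trial as it was randomised, and adding the stratum is a free improvement. For the t-test comparisons, over an assumed R² of 0 to 0.10, type I error is 5.0% down to about 3.9% (3.7% to 4.0% simulated at the upper end), intervals are 0 to 5% too wide, and adjustment gains 0 to about 2 percentage points of power at 60 per group. If the inclusion group does not predict GIQLI change, nothing is lost.

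A reader might infer that the planned t-test is invalid. It is not: the error is in the conservative direction, the estimated mean difference is unbiased, and false positives are not inflated by this omission.

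The figures rest on the assumed R², on SD 22 as the total within-arm SD of the change, and on near-exact balance within strata. The Randomization section intends such balance but does not describe how it is achieved; with looser balance the t-test would be less conservative.

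**What to change.** 1. **Primary outcome and normally distributed continuous outcomes.** Replace the t-test with a linear model containing treatment arm and the inclusion group used at randomisation (three levels) as a fixed factor. Report the adjusted mean difference with its 95% confidence interval.
2. **Stratum definition.** A patient may meet more than one criterion, and the protocol gives no rule for that case. State that the analysis uses the stratum entered at randomisation. The protocol does not say that this value is stored, but it must be supplied for the allocation to be stratified, so confirm that it can be retrieved.
3. **Binary outcomes with enough events.** Use a stratified (Mantel-Haenszel) analysis, and note that its odds ratio is a different quantity from the crude one. Set beforehand what counts as enough events.
4. **Rare binary outcomes.** Keep exact methods. Deaths, stomas, emergency operations and fistulas may be too few to split over three strata in about 120 to 133 patients.

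No event-time method is needed, because the plan contains no such analysis. The cost is a few sentences in the analysis plan and two degrees of freedom, with no extra patients and no new data collection if the stratum can be retrieved.

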## Intervention

### 1. Elective laparoscopic sigmoid resection

The patient is scheduled for elective laparoscopic sigmoid resection. Surgery is performed within a maximum of 3 months of randomisation. CRF # 3 is filled just before surgery (e.g., during a preoperative visit). CRF # 2 is filled as the patient is discharged after elective sigmoid resection. After the operation, the patient is given lifestyle instructions as well as a recommendation for the use of a fiber supplement.

## Technique of laparoscopy

1. Port setting free
2. Distal resection site in the upper rectum, below the promontory
3. Proximal resection site in oral sigmoid or descending colon
4. Splenic flexure is mobilized as needed to obtain a tension-free anastomosis.
5. The aim is to keep the blood vessels as good as possible. A. mesenterica inferior and A. Rectalis superior are sought to be spared. However, if necessary, the blood vessels can be ligated, for example to provide a non-tight anastomosis or if the dissection conditions are difficult.
6. Bowel anastomosis with ILS.

## 2. Conservative treatment

### Lifestyle guidelines in writing

- Duodecim Medical Publications Information to the patient: The intestinal diverticular disease, 12/11/2012

Pertti Black River ([www.terveysportti.fi](http://www.terveysportti.fi))

- Medical book Duodecim Information for the patient: Constipation 8.10.2012 Pertti Mustajoki

([www.terveysportti.fi](http://www.terveysportti.fi))

Recommendation on the use of fiber supplement.

Action in the event of elective sigmoid resection in a patient randomized to conservative treatment:

Conservative treatment should be tried for at least 6 months of randomisation (= until the first quality of life survey) before it can be concluded that it has failed and the patient referred to elective sigmoid resection. Of course, surgical treatment can be performed earlier if the patient has developed absolute indications for elective sigmoid resection (eg fistula, stricture). If a patient randomized to conservative treatment has to be treated with elective sigmoid resection, the patient should complete the GIQLI and SF-36 quality of life questionnaires at the time of surgery. After surgery, the patient is followed according to the original follow-up schedule (i.e., surveys just before surgery (preoperative visit, etc.), 6 months, 12 months, 24 months, 48 months, and 96 months after the initial randomisation). In accordance with normal research ethical principles, the patient may also opt out of the study altogether, at which point his or her follow-up will cease and he or she will be treated according to normal treatment lines and at the discretion of the attending physician.

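### Opting out ends all data collection, so patients who leave before month 6 drop out of the primary analysis and the intention-to-treat result becomes a completer t-test

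*Supplement*

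**What the plan says.** All references are to the latest protocol, which carries the analysis plan amended on 5 August 2020.

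- **Leaving the study.** Section 2, Conservative treatment: "the patient may also opt out of the study altogether, at which point his or her follow-up will cease". Care then follows usual practice at the treating physician's discretion.
- **Surgery in the conservative arm.** Same section: "Conservative treatment should be tried for at least 6 months of randomisation (= until the first quality of life survey". The exception is that "surgical treatment can be performed earlier if the patient has developed absolute indications for elective sigmoid resection".
- **Crossover inside the study.** Same section: "After surgery, the patient is followed according to the original follow-up schedule". These patients remain in follow-up and in their randomised group.
- **Primary outcome.** GIQLI, "difference between 0 months and 6 months from randomisation".
- **Analysis.** The analysis plan compares the primary outcome by t-test with a mean difference and 95% confidence interval, and states: "All outcomes will be analyzed using intention-to-treat principle where patients are analyzed in the group where they were randomized to". It has no rule for a missing 6-month score, no covariate adjustment and no sensitivity analysis.
- **Loss.** The sample size section: "Approximately 10% of patients are estimated to disappear at follow-up". This raises the total to 133 and is not divided by arm or reason.

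**The concern.** A change score from 0 to 6 months needs both questionnaires. A patient who opts out before month 6 has only the first, and the protocol stops looking for the second. The intention-to-treat sentence settles which group a patient is counted in. It does not say what happens when there is no outcome to count.

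This matters more than ordinary attrition because the design gives the two arms different reasons to leave. Surgery patients are to be operated on within 3 months of randomisation. Conservative patients without an absolute indication are expected to wait until month 6, which is also the primary time point. A dissatisfied conservative patient therefore has a motive to leave that the surgery arm does not share. If leaving is related to quality of life, the patients who remain are no longer the randomised groups, and raising the number recruited does not repair that.

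**Working it through.** **1. The plan's own figures.** The inflation reproduces: 120 / 0.9 = 133.3, stated as 133. The 60 per group does not: 2 × (1.960 + 1.282)² × 22² / 12² = 70.6, so 71 per group for two-sided 90% power (72 with the t distribution). Sixty per group gives 84.2%. That is a separate matter. What counts here is that the 10% enters only as a divisor.

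**2. Bias formula.** Suppose a fraction p of the conservative arm leaves before month 6. Let g0 and g6 be the stayers' mean minus the leavers' mean (the latter as it would have been) at baseline and at month 6. Stayers overstate the arm's baseline mean by p × g0 and its 6-month mean by p × g6. The bias in surgery minus conservative is therefore:

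- change score: p × (g0 − g6)
- 6-month score adjusted for baseline: about p × (ρ × g0 − g6), with ρ the baseline-to-6-month correlation

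Assumptions, none of them in the documents: ρ = 0.5 (with SD 22 at both times, the SD of change is 22 × √(2 × 0.5) = 22, the plan's value); p = 0.09 to 0.10; the gaps used below; no selective loss in the surgery arm.

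**3. Three reasons for leaving.**

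| Leaving driven by | Relation | Change-score bias | Baseline-adjusted bias |
|---|---|---|---|
| Low baseline, g0 = 15 to 22, p = 0.09 | g6 = 0.5 × g0 | 0.09 × 0.5 × 15 = 0.7 to 0.09 × 0.5 × 22 = 1.0, **towards** surgery | 0 |
| Poor 6-month status, g6 = 15, p = 0.09 | g0 = 0.5 × g6 | 0.09 × 0.5 × 15 = 0.7, **against** surgery | 0.09 × 0.75 × 15 = 1.0, against |
| Worsening, gap in change 15 to 20, p = 0.10 | g6 − g0 = 15 to 20 | 1.5 to 2.0, **against** surgery | not removed |

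The first row is regression to the mean: patients who start low tend to improve more, so losing them lowers the conservative arm's mean change. Simulation of about 9% baseline-dependent loss (ρ = 0.5, SD 22, true effect 0) agrees: bias of about 0.7 to 1 point towards surgery on the change score, and about zero after baseline adjustment.

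**4. Effect on the test.** The planned loss is about 13 of 133. Take arms of 66 conservative and 67 surgery, with conservative leavers 15 points worse in change.

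- Losses 7 and 6: 7/66 × 15 = 1.59. A true 12 is estimated as 10.41, and power falls from 84.2% to 72.9%. With no true difference, rejection is 6.8% instead of 5%.
- All 13 losses conservative (an extreme split): 13/66 × 15 = 2.95. A true 12 becomes 9.05, power falls from 83.7% to 60.2%, and null rejection is 11.2%.

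**The case against.** The right to withdraw is proper, and the protocol presents it as ordinary research ethics. It already distinguishes a conservative patient who is operated on within the study, who stays in follow-up and in the randomised group, from one who leaves the study entirely. Both points stand. They narrow the problem to full withdrawals but do not say what is done about their missing scores.

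A reader might infer that opting out is the only way to earlier resection. The documents do not go that far. "Conservative treatment should be tried for at least 6 months of randomisation" is a recommendation, the listed absolute indications are examples, and at 6 months a telephone call can lead to in-study referral. No section links opting out to seeking surgery.

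A reader might also infer that the bias must run against surgery. It need not: the low-baseline case runs the other way. Surgery patients may withdraw too, for instance by declining the operation or after a poor recovery, and losing poorly recovering surgical patients would flatter surgery. Arm-specific loss is plausible from the design but not shown.

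Finally, the gaps are assumed, and at the planned loss the bias is modest next to 12 points. That is fair, and it limits the severity.

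**Conclusion.** The point holds as a gap in data collection and analysis, not as a demonstrated bias. Follow-up stops on opting out, the primary outcome needs a 6-month score, and the stated test cannot use patients without one. The promised intention-to-treat analysis is thus a completer analysis for anyone who leaves before month 6. That the t-test runs on completers is inferred from the method and the absence of any missing-data rule, but no other reading of a t-test on change is available.

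Under the stated assumptions the distortion is roughly 0.7 to 1 point towards surgery if leaving tracks low baseline, and about 0.7 to 2 points against surgery if it tracks poor 6-month status or worsening, at 9 to 10% conservative-arm loss. Two points is 2/12 = 17% of the target difference. The number, timing, arm and reasons of opt-outs are not in the documents, so neither sign nor size can be fixed in advance. This should be changed; it does not invalidate the design.

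**What to change.** 1. **Keep collecting data.** Separate leaving the allocated treatment from refusing further data. Ask patients who leave to go on returning the GIQLI and SF-36 that are already mailed, at least at 6 months, and to allow record review, unless they refuse this. Record the date of and reason for leaving, by arm.
2. **Adjust the primary analysis.** Analyse 6-month GIQLI by randomised group with adjustment for baseline GIQLI and the inclusion-criterion stratum. This removes bias from baseline-dependent loss. It does not remove bias from loss driven by later status, as the table shows, so the other two steps are still needed.
3. **Add a delta-adjusted sensitivity analysis.** For patients without a 6-month score, vary the assumed shortfall separately by arm and report how large it must be to change the conclusion.

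A mixed model is optional. Month 6 is the first scheduled survey for an unoperated conservative patient, so someone who leaves before it has only a baseline score, and the model recovers nothing for that patient.

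The cost is a change to consent and protocol wording, a few more postal forms and a standard regression. Some patients will still refuse all contact. No rule on who is operated on, or when, is altered.
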